### Data collection

The Credibility/Expectancy Questionnaire, Case Report Form, TCM Diagnosis Form and Adverse Events Form are completed on paper copies. All other outcome measures, participant characteristics and risk factors for hot flushes are completed online using a survey management website (Survey Methods http://www.surveymethods.com), with paper copies available for those who prefer to use them. Online surveys have the advantage of minimising missing data if completion of survey questions is made mandatory prior to submitting the survey online. Range checks are also built into online surveys, and automated reminders are Emailed. The study acupuncturist and research assistant (CE and KN) oversee this data management. A reminder letter/Email is sent after two weeks, followed by a courtesy telephone call two weeks later by the research assistant should questionnaires not be returned. Details of treatment dates and follow-up are recorded in a custom-built password-protected database.

All paper-based data are entered into the same survey management website by staff blinded to group allocation at the University of Melbourne. Ten percent of all data entry will be audited by an independent investigator for quality assurance purposes.

### Statistical methods

Descriptive statistics will be used to summarise baseline measures and participant characteristics between the two trial groups and to assess for chance imbalance of important prognostic factors. Primary outcome is the hot flush score at EOT. Analysis will account for repeated outcome measures taken on the same women over 12 months and stratification by project acupuncturists. Mixed-effects linear regression model will be used to compare the continuous outcomes between the trial groups and marginal logistic regression model using generalised estimating equations with robust standard errors will be used for the binary outcomes. Where appropriate the baseline measure of the outcome will be included as a covariate in the regression model. In addition, factors strongly associated with the outcome and are found to be imbalanced between the trial groups at baseline will also be adjusted in the regression models. Estimates of the intervention effect will be reported as the difference in means between trial groups for continuous outcomes and odds ratios for binary outcomes, with respective 95% confidence intervals and *P*-values. Stata 13.0 [70] will be used for the data analyses.

An intention-to-treat analysis strategy will be employed where all participants will be analysed in the trial group in to which they were allocated [71]. In the first instance, we will strive to minimise the extent of missing outcome data for participants, where all efforts will be made to collect the primary outcome on participants who withdraw, discontinue their treatment or do not respond to the online survey. However, in the presence of incomplete data, information collected on the reasons for missing data will be used to inform the appropriate statistical analysis approach to handle the missing data. Sensitivity analyses that capture departures from the assumption of the missing data mechanism for the primary analysis will also be considered to assess the robustness of the results.

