### Sample size calculation

Sample size calculations are based on a two-sample *t*-test with 80% power and significance level at 5% for a two-sided test. We assumed conservatively that the mean hot flush score at baseline would be 14, the lowest possible entry score for the trial. Assuming a 50% relative reduction in the HF scores in the control group due to the placebo effect, which is the typical response reported in hot flush randomised controlled trials [69], we anticipate that women in the sham acupuncture group will have a mean hot flush score of 7 at EOT. To be clinically significant, we expect that women in the true intervention group to show at least 75% reduction in the total HF score from baseline, with a mean HF score of 3 at EOT. Based on these assumptions, 266 women (133 per trial group) will be needed to detect hot flush score difference of 4 (standard deviation (SD) = 11.6 [51]) between the two trial groups at EOT. This sample size is sufficient to detect a difference of 0.35 of 1 SD between the trial groups for the quality of life measures. Sample size was inflated to 360 women (180 per study group) to allow for attrition of 26% (experienced in the pilot study) at the measurement of the primary outcome at the EOT.

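### The covariates of the primary model depend on which baseline factors turn out imbalanced in the trial's own data, so the main analysis is not fixed in advance

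*Protocol article*

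**What the plan says.** All in the protocol article:

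- Statistical methods: baseline summaries by group serve "to assess for chance imbalance of important prognostic factors". The section then says "Primary outcome is the hot flush score at EOT" and plans a mixed-effects linear model that accounts for repeated measures and for stratification by project acupuncturist.
- Same section, on baseline: "Where appropriate the baseline measure of the outcome will be included as a covariate in the regression model".
- Same section, on further covariates: "factors strongly associated with the outcome and are found to be imbalanced between the trial groups at baseline will also be adjusted". No factor is named, neither strength of association nor imbalance has a threshold, and nothing makes this adjustment secondary.
- Participants' characteristics and risk factors for hot flushes: twelve items are collected at enrolment, most with literature citations. None is fixed as a covariate.
- Sample size calculation: a "two-sample *t*-test with 80% power and significance level at 5% for a two-sided test", with no allowance for covariate adjustment.
- Blinding: the analysis is done on coded groups, and the codes are revealed after the six-month data are complete.

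**The concern.** In a randomised trial a baseline difference between groups is a chance event. A covariate is useful because it predicts the outcome, and that does not depend on whether it happens to differ between groups. A rule triggered by observed imbalance has three consequences:

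- The form of the primary model cannot be stated before the data are examined.
- The confidence interval and P-value are computed as if the chosen model had been the only candidate.
- With no threshold, two analysts following the text faithfully could report different adjusted results, or one adjusted and one not.

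The qualifier on the baseline term adds a further uncertainty. If it were taken as permission to leave baseline hot flush score out of the primary model, the trial would give up precision available from data it already holds.

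**Working it through.** **1. The plan's own figure.** The inputs from Sample size calculation are a difference of 4, SD 11.6, two-sided 5% and 80% power.

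- n per group = 2 × (1.960 + 0.842)² × 11.6² / 4² = 132.02, rounded up to 133. This matches "266 women (133 per trial group) will be needed".
- With 26% attrition: 266 / 0.74 = 359.5, rounded up to 360. This also matches.
- The exact t-test power at 133 per group is 80.0%; the normal approximation used in step 2 gives 80.3%.

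**2. What leaving baseline out would forgo.** With baseline as a covariate the residual SD is 11.6 × √(1 − r²), where r is the correlation between baseline and end-of-treatment score. The article gives no r, so 0.3 to 0.7 is assumed. Power = Φ(4 / (SD × √(2/133)) − 1.96).

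| r | Residual SD | CI width relative to unadjusted | Power | Gain over 80.3% |
|---|---|---|---|---|
| 0.3 | 11.07 | 0.95 | 83.8% | 3.5 points |
| 0.5 | 10.05 | 0.87 | 90.1% | 9.8 points |
| 0.7 | 8.28 | 0.71 | 97.6% | 17.3 points |

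**3. The imbalance rule applied mechanically.** A simulation used 133 per group and 6,000 runs per setting. The assumptions are 11 independent candidate factors, each correlated 0.15 with the outcome, and a factor entering if both imbalance and association reach P<0.05. The outcome is a single end-of-treatment score analysed by linear regression, so repeated measures and acupuncturist strata are left out.

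**4. The freedom the wording leaves.** In the same runs, the smallest P-value was taken over four models: baseline in or out, selected factors in or out.

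| r | Type I, baseline only | Type I, baseline + rule | Type I, smallest of four | Power at 4, baseline only | Power at 4, baseline + rule |
|---|---|---|---|---|---|
| 0.3 | 4.9% | 4.2% | 6.7% | 83.9% | 84.6% |
| 0.5 | 5.0% | 4.1% | 7.9% | 89.5% | 90.0% |
| 0.7 | 5.1% | 3.8% | 9.4% | 97.4% | 98.0% |

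The simulation error near 5% is √(0.05 × 0.95 / 6000) = 0.28 points. At least one factor was selected in 30% to 33% of simulated trials, so the adjusted set did vary by chance. With a looser imbalance threshold of P<0.2 (r = 0.5), the figure was about 80%, type I error under baseline plus rule was 3.5%, and the smallest of four gave 8.8%.

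**5. A second setting.** Here baseline is always in and one further factor is subject to the rule, with 4,000 runs. The assumed correlations are 0.3 or 0.5 for baseline and 0.15 or 0.3 for the factor. Power at a difference of 4 was 83% to 90% under the rule, against 84% to 92% when both were always adjusted, a gap of about 1 to 3 points. Type I error was 4.6% to 5.2%.

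**The case against.** The strongest reply has four parts.

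- **Baseline is probably in the model.** The sentence on the baseline measure governs every outcome, and some outcomes have none: credibility/expectancy is measured once, after the first treatment. The qualifier therefore reads naturally as referring to outcomes that have a baseline value, and the hot flush score has one. This stands. It makes the power loss conditional, and it removes two of the four models in step 4. The 7% to 9% therefore belongs to the looser reading; the run did not isolate the inflation with baseline always included.
- **The rule itself does no measurable harm to error rates.** This also stands. Applied mechanically it was neutral or slightly conservative and cost little power.
- **Analysis on coded groups limits steering.** This stands in part. Coding hinders choosing a direction, but it does not fix the model or prevent a choice of the smaller P-value.
- **Covariate lists belong in a statistical analysis plan that is not shown.** The absence of a list is indeed no finding. However, the article does more than stay silent: it states a positive rule for the main models, and a plan that followed the article would inherit it.

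Strength of association might also mean association known beforehand from the cited literature. That reading is open. Imbalance, by contrast, can only be found in the trial's own data.

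**Conclusion.** The point holds in a limited form. The primary model is data-dependent by stated rule, its trigger is undefined, and the reported interval and P-value take no account of the selection. The size depends on how the freedom is used: none or slight conservatism if the rule is applied mechanically, and about 7% to 9% type I error if the best of four permitted models were reported. Both results rest on the assumed correlations and thresholds.

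Three stronger inferences are tempting but not supported:

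- **That the plan loses power.** Nothing says baseline score will be dropped. If it were, the loss of about 4, 10 or 17 points is relative to a fixed baseline-adjusted model. The planned 80% rests on an unadjusted test and is kept.
- **That power is near 70% because of this rule.** Unadjusted power is about 69% at a difference of 3.5, the value that follows if a 75% reduction from 14 is taken as 3.5 and set against 7. That concerns the sample size inputs, not covariate choice.
- **That the rule would be triggered in 46% of trials** (1 − 0.95¹² for twelve independent factors at P<0.05), or 72% at P<0.10. The article states no P threshold and requires strong association as well as imbalance, and the factors are unlikely to be independent.

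**What to change.** Before the group codes are revealed:

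1. Keep the planned repeated-measures mixed model.
2. State that baseline hot flush score and project acupuncturist are always in the primary model.
3. Add, if wanted, only a short list of prognostic factors already collected, named in advance and included whatever their observed balance. BMI, smoking status and HADS anxiety are examples.
4. Move any imbalance-driven adjustment to a sensitivity analysis labelled as such.

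The cost is wording only. No new data, sample size change or change of model class is needed.

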#### Secondary analyses

Additional secondary analyses are planned. These will include (1) exploring the effect acupuncture had on women’s quality of life, (2) identifying factors that are associated with a placebo response, (such as anxiety/depression levels and demographic characteristics such as socioeconomic status), (3) the association between expectancy and beliefs and women’s response to acupuncture treatment, and (4) the credibility of the Park Sham Device.

### Data monitoring

As acupuncture has an excellent safety profile, and is not considered an experimental treatment, no data monitoring committee is required.

## Discussion

Hot flushes are a common and potentially disabling symptom during the menopause. While HRT is an effective treatment, it does not suit all women either because of concerns over potentially serious adverse events, or because of relative contra-indications. Many women also prefer to use natural or complementary therapies where available. There is a paucity of effective and safe non-hormonal treatments for VMS. However, preliminary evidence suggests that acupuncture, a popular and safe treatment for a wide range of conditions, may be effective for VMS.

We are conducting a randomised sham-controlled trial on acupuncture for VMS, which builds on the results from our earlier pilot project during which feasibility of methods was demonstrated. This robustly designed study meets methodological benchmarks of adequate randomisation and allocation concealment procedures, blinding of outcome assessors and statisticians and utilising intention-to-treat analysis strategy. The trial method also allows for Traditional Chinese Medicine diagnosis in the eligibility criteria and a ‘dose’ of acupuncture reflecting clinical practice to ensure results are applicable to a broad range of health practitioners. The trial is appropriately powered to determine a clinically relevant treatment effect. Our results will determine the efficacy of acupuncture for treating VMS in postmenopausal women. In particular, we will assess the specific effect of insertion of the acupuncture needle and its contribution to the entire treatment effect.

Our results will inform women suffering with menopausal symptoms and both conventional and Traditional Chinese Medicine health care professionals on the potential role, if any, of acupuncture in the treatment of VMS. This will advance the field significantly and, if effective, will offer an important treatment option to reduce VMS and potentially improve quality of life in women at this important life stage. Future research may explore the optimal treatment regimen for acupuncture for VMS.

## Trial status

The trial has received funding and recruitment commenced in late 2011. At the time of submission of this protocol, project acupuncturists had been trained, participant enrolment was progressing well and data collection was well underway. Trial enrolment closed in March 2014. We anticipate that all data will be collected by late 2014.

## Abbreviations

BMI: body mass index; CM: complementary medicines; CONSORT: Consolidated Standards of Reporting Trials; EOT: end-of-treatment; FSH: follicular stimulating hormone; HADS: Hospital Anxiety and Depression Scale; HFD: Hot Flush Diary; HRT: hormone replacement therapy; MENQOL: Menopause-specific Quality of Life questionnaire; STRICTA: Standards for reporting interventions in acupuncture trials; RCT: randomised controlled trial; SD: standard deviation; SNRIs: serotonin-noradrenaline reuptake inhibitors; SSRIs: selective serotonin reuptake inhibitors; TCM: Traditional Chinese Medicine; TNZ: thermoneutral zone; VMS: vasomotor symptoms.
